#### Inclusion criteria for patients

Patients aged 18 or over who have a diagnosis of stroke based on the WHO criteria [36] will be included in the study, with no upper age limit. Patients are required to have urinary incontinence (UI) as defined by the International Continence Society [37] as "involuntary loss of urine" and to have incontinence classified as stress UI, urge UI, mixed UI or 'functional' UI **OR **to be catheterised in the acute phase of the stroke; to be conscious (defined as either 'alert' or 'drowsy' on the 'Clinical Status on Admission' item of the European Stroke Database), and to be medically stable as judged by the clinical team.

Participants who had incontinence before the index stroke will be included. Given the expected age range of the population, there is likely to be a high prevalence of pre-stroke incontinence among potential participants. Furthermore, there is evidence to suggest patients with longstanding incontinence may benefit from a programme of behavioural interventions [9,11].

Participants who are catheterised will be recruited; if the catheter is removed, they will be assessed as per protocol and begin the systematic voiding programme if they are still incontinent. Participants who are continent after catheter removal and those discharged with a catheter still in situ will not be put onto the programme. Data from these participants will be analysed separately from participants who have taken part in the programme.

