### Patient recruitment process

Patients who meet the inclusion criteria will be approached as early as possible following admission to the participating stroke unit. Patients who do not meet the inclusion criteria early post-stroke will be approached as soon as possible if they subsequently meet the inclusion criteria. Nursing staff will ask each eligible patient whether his/her name can be given to the research team. If the patient agrees, a member of the research team will visit the patient, explain the project, answer any questions they may have and provide an information leaflet. Patients will be given at least 24 hours to consider participation and will be visited by a member of the research team after this period; patients choosing to participate will sign the consent form at this stage.

For patients unable to consent for themselves, a person able to advise on the presumed wishes of the patient will be approached to act in the role of consultee. This is in line with the recommendations of the Mental Capacity Act [38] and in line with the expressed wishes of the study Patient, Public and Carer Involvement groups, who would like everyone who is eligible to have the opportunity to participate.

Recruitment rates in each cluster will be monitored on a monthly basis to identify both quantitative (i.e. numbers of participants recruited) and qualitative (i.e. patient characteristics) imbalance across clusters [39]. Should identified imbalance be indicative of likely selection bias (e.g. cluster with low proportion of stroke patients identified as eligible but high proportion of those eligible with severe incontinence), we will review the recruitment process and address any issues identified.

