### Outcomes

#### Effectiveness

The primary effectiveness outcome will be incontinence (presence; absence). Measures will be taken at 6 weeks, 3 months and, for those recruited during the first three months, 12 months post stroke. The primary analysis will be of the 6-week data as conservative interventions for continence typically last six weeks [11,15], and an effect is most likely to be seen at this time point.

Secondary effectiveness outcomes will be: quality of life, frequency and severity of incontinence, urinary symptoms, activities of daily living (ADLs), and death; at 6 weeks, 3 months and, for those recruited during the first three months, 12 months post stroke.

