#### Ascertainment of outcomes

Presence/absence of incontinence will be measured by the International Consultation on Incontinence Questionnaire (ICIQ-UI Short Form) [51]. Absence of incontinence will be defined as the response 'never' to Question 3, 'How often do you leak urine?'; presence of incontinence will be defined as any other response to Question 3 (ranging from 'about once a week or less often' to 'all the time'). The ICIQ-UI Short Form has received a grading of A^new ^- highly recommended from the International Consultation on Incontinence Symptoms and Quality of Life Committee indicating published reports of acceptable reliability, validity and responsiveness in at least one study [52]. To our knowledge, the ICIQ-UI Short Form has not been used in the post-stroke population. We have conducted preliminary validation of the tool with six stroke survivors from our Patient, Public and Carer Involvement Group using the approach recommended by the ICIQ developers ([name], personal communication); all thought the tool was appropriate for use post-stroke and few problems were identified.

Quality of life will be measured using the Incontinence Quality of Life Instrument (I-QOL) [53,54] and the EuroQol (EQ-5D) [55]. Frequency and severity of incontinence will be ascertained using the Incontinence Severity Index [56]. Urinary symptoms will be measured using the Leicester Urinary Symptom questionnaire [57] and activities of daily living via the Barthel Index [58].

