In addition, the following baseline information about the patient will be recorded following consent: date of birth (age to be calculated*); sex; ethnicity; date of admission; date of stroke onset; date baseline questionnaire completed; location when recruited into the study; consciousness level (defined as either 'alert' or 'drowsy' on the 'Clinical Status on Admission' item of the European Stroke Database); side of body affected by stroke; type of stroke; location of stroke (OCSP classification[59]); co-morbidities (Charlson Comorbidity Index[60]; day seven Barthel Index [58]; pre-stroke Modified Rankin Scale [61]*; pre-stroke living circumstances*; Leicester Urinary Symptom questionnaire [57]; type of UI (urge UI, mixed UI, 'functional' UI or unclear); cognitive ability (6 Item Cognitive Impairment Test [62]); fluid intake; bowel function; relevant clinical investigations (e.g. mid stream urine, bladder scan); medications; living circumstances; verbal sub-section of the Glasgow Coma Scale [63]*; ability to lift both arms off the bed*; ability to walk independently*; ICIQ-UI Short Form [51]; Incontinence Severity Index [56]; EuroQol (EQ-5D) [55].

The six factors highlighted with a * above from the Edinburgh stroke case mix adjuster [64] will be collected to enhance patient-level adjustment for prognosis.

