#### Outcomes

The primary analysis set will be defined as the intention-to-treat population. All stroke services randomised will be retained in the trial. Outcome data will be collected from all consented patients whenever possible, whatever their level of subsequent engagement with the allocated intervention programme. If there is more than 10% loss to follow-up overall or moderately differential loss to follow-up across stroke services, a secondary per-protocol analysis will also be considered. The decision as to whether a per-protocol analysis will be informative will be made by the trial statistician in conjunction with other members of the Trial Management Group; this decision will be made without reference to the recorded values of the outcome data.

To account for the cluster randomisation, we shall use mixed effects modelling for continuous, ordinal and dichotomous outcomes to compare the two groups on primary and secondary outcome data. Baseline measures of the outcomes variables (where appropriate), stroke classification, type of incontinence and the other prognostic patient-level information (from the Edinburgh case-mix adjuster) will be included as individual-level covariates in the models for outcome data.

Missing outcome data will be imputed according to the particular outcome. For the primary analysis, dichotomous and ordinal outcomes for those who withdraw, die or are otherwise lost to follow-up will be imputed using a worst-case scenario (e.g. for the primary outcome variable, all those for whom incontinence status is not recorded at 6-weeks post-stroke will be assumed to be incontinent). For continuous outcomes, the primary analysis will use a non-parametric multiple imputation approach [66].

The effect of stroke service-level factors will also be explored in the modelling; this will enable appropriate stratification to be used in the future larger scale trial, if desired, and to potentially reduce the size of the intra-stroke service correlation coefficient by reducing the unexplained component of the variability between stroke services. This analysis will be used to confirm the sample size necessary for the future trial and to provide estimates (including 95% confidence intervals) of the effectiveness of each intervention relative to usual care.

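### The baseline value of the binary primary outcome cannot adjust for incontinence severity, and the primary model names no graded baseline measure, although two are collected

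*Protocol article*

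**What the plan says.** **Outcome.** Under Effectiveness, "The primary effectiveness outcome will be incontinence (presence; absence"), with the primary analysis at six weeks. Ascertainment of outcomes sets the cut: "Absence of incontinence will be defined as the response 'never' to Question 3, 'How often do you leak urine", while "presence of incontinence will be defined as any other response to Question 3".

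**Entry.** Under Inclusion criteria for patients, "Patients are required to have urinary incontinence (UI) as defined by the International Continence Society"; the alternative route is catheterisation in the acute phase.

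**Model.** Under Data analysis, Outcomes, the individual-level covariates are "Baseline measures of the outcomes variables (where appropriate), stroke classification, type of incontinence and the other prognostic patient-level information (from the Edinburgh case-mix adjuster"). By the starred items in the baseline list, the Edinburgh factors are age, pre-stroke Rankin score, pre-stroke living circumstances, verbal Glasgow Coma Scale, arm lift and independent walking.

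**Baseline data.** The same list ends with "ICIQ-UI Short Form [51]; Incontinence Severity Index [56]; EuroQol (EQ-5D) [55"], so both the primary outcome's instrument and a severity index are recorded at entry.

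**Selection.** Allocation concealment states that, once allocation is released, staff who identify and recruit participants know it. Patient recruitment process gives as its example of likely selection bias a "cluster with low proportion of stroke patients identified as eligible but high proportion of those eligible with severe incontinence".

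**The concern.** Adjusting an outcome model for the baseline value of the outcome is normally the strongest protection available against prognostic imbalance. Here the entry rule removes the information from that baseline value: nearly everyone who can be assessed starts in the same category of a two-category variable. What differs between participants at entry is how often and how badly they leak, and no covariate named for the primary model measures that directly.

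This matters more than in an individually randomised trial, because participants are enrolled after their service's allocation is known. If one arm enrols milder cases, more of them may be dry at six weeks whatever the treatment, and some of that difference would be read as an intervention effect. Unmodelled severity differences between services would also add to the between-service variance. The pilot is meant to estimate that variance for planning the full-scale trial.

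**Working it through.** The protocol gives no severity mix, no six-week continence rate by severity and no share catheterised, so there is no figure of its own to reproduce. The check is first logical, then illustrative.

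**1. What the baseline term contains.**
- Incontinence route: incontinence is required at entry, and the outcome counts any Question 3 answer other than 'never' as present. The baseline indicator is 1 by the entry rule. A column of ones is collinear with the intercept, so it cannot be fitted and adjusts for nothing.
- Catheter route: leakage may not be assessable, or may be answered 'never', while the catheter is in place. The indicator can then vary, but what it records is catheter status, not severity.

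**2. What the other named covariates contain.**
- Type of incontinence: a category (urge, mixed, functional or unclear in the baseline list), not a grade.
- Stroke classification and the six Edinburgh factors: stroke type, function and case mix. They may correlate with incontinence severity but do not measure it.
- The strata for randomising services (unit structure, audit performance, admissions) do not use severity either.

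**3. Size of a possible bias (all inputs assumed).** With no true effect and a binary severity factor, spurious risk difference = difference between arms in the share severe × difference in six-week continence between mild and severe cases.

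| Imbalance in share severe | Prognostic difference | Spurious risk difference |
|---|---|---|
| 0.10 | 0.20 | 0.020 |
| 0.15 | 0.25 | 0.0375 |
| 0.20 | 0.30 | 0.060 |

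On the odds-ratio scale, take a reference arm that is half severe:
- Incontinence 70% if severe and 50% if mild, 10-point imbalance: 0.60 against 0.58, odds ratio (0.58/0.42)/(0.60/0.40) = 0.92.
- Incontinence 80% if severe and 50% if mild, 20-point imbalance: 0.65 against 0.59, odds ratio (0.59/0.41)/(0.65/0.35) = 0.77.

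**4. What each kind of covariate would remove.** A large-sample logistic simulation used 300,000 patients, no clustering and no true effect. It assumed severity 0.3 SD lower in one arm and a log-odds of 0.8 per SD of severity. Catheter status was drawn independently of severity and arm. The true odds ratio is 1.

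| Adjustment | Estimated odds ratio |
|---|---|
| None | 0.80 to 0.83 |
| Binary baseline, nobody catheterised | cannot be fitted |
| Binary baseline, 20% or 40% catheterised and coded 'never' | 0.80 to 0.82 |
| Proxy correlated 0.3 with severity | 0.81 to 0.84 |
| Proxy correlated 0.5 | 0.85 to 0.86 |
| Proxy correlated 0.7 | 0.88 to 0.90 |
| Baseline severity itself | 0.99 to 1.02 |

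Under these assumptions the binary baseline changes nothing, correlated covariates help in part, and a direct severity measure removes the bias.

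**The case against.** **The wording is flexible.** The baseline clause covers outcomes of every type and is qualified by 'where appropriate', so a constant term may simply be dropped. It refers to outcome variables in the plural, and severity is itself a listed secondary outcome, so the clause could be read to admit the Incontinence Severity Index or a graded ICIQ score. This stands: the text is open rather than plainly wrong. But dropping the term leaves no severity covariate, and the qualifier has an ordinary use elsewhere (death has no baseline value, and I-QOL is not in the baseline list). A permissible reading is not a commitment.

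**It belongs in the analysis plan.** An analysis plan is to be finalised before outcome data reach the trial statistician, and it may name a graded measure. This limits the point. The article does, however, state a specific covariate list, and it is that list which sits badly with the entry rule.

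**The risk is managed elsewhere.** Recruitment is monitored monthly, the link between eligibility rate and mild incontinence is examined every three months, and baseline data are tabulated by arm and by cluster. These steps would show an imbalance and could change later recruitment. They do not adjust for severity among patients already enrolled, and the listed sensitivity analyses do not include that adjustment.

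**Other covariates help, and the pilot is imprecise.** Partial absorption by the remaining covariates is plausible; how much is unknown. With 780/3 = 260 per arm and an assumed 50% incontinence, the 95% half-width of a risk difference is 1.96 × √(2 × 0.25/260) = 8.6 points before clustering. With 780/12 = 65 per service and an assumed intra-class correlation of 0.02, the design effect is 1 + 64 × 0.02 = 2.28 and the half-width about 13 points. The illustrative bias is smaller than either, but imprecision does not excuse an avoidable bias.

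**Conclusion.** The point holds in a limited form. For incontinence-route participants, the baseline value of the binary primary outcome carries no severity information. No other covariate named for the primary model measures severity directly, and the article does not commit to a graded measure that it already collects.

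A reader might infer more: that the planned adjustment does nothing at all, and that any severity imbalance stays whole in the effect estimate. The documents do not support that. Catheterised entrants mean the baseline is not strictly constant, the other covariates may absorb part of an imbalance, and the qualified wording leaves room for a graded measure. Nor do the documents show that an imbalance will occur; severity is given as an example of what to watch for.

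The 2 to 6 percentage points rest wholly on the assumed 10 to 20 point imbalance and 20 to 30 point prognostic difference, before partial adjustment by the other covariates. The change is worth making because it costs little and addresses a threat the protocol itself names.

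**What to change.** In the covariate list for the primary model, name one graded baseline severity measure: the ICIQ-UI Question 3 frequency category or the Incontinence Severity Index. Code participants who are catheterised at entry as a separate level of that covariate. Use it in place of the present/absent baseline value, and keep the other listed covariates. Report the estimate without the severity covariate as a sensitivity analysis, so that readers can see how far severity imbalance moves the result.

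The cost is wording in the analysis plan. Both measures are already collected at baseline, and catheter status is known from the route of entry. The downside is one extra patient-level covariate with a few levels.

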### Objectives

The trial objectives are to:

• assess feasibility in terms of rates of participant recruitment and retention

• assess fidelity to the intervention

• conduct a qualitative assessment of feasibility from the perspective of multiple stakeholders

• conduct a preliminary evaluation of supported implementation compared with implementation alone

• investigate patient-related factors affecting patient outcome

• investigate stroke service-level factors potentially affecting stroke service outcomes to estimate the amount of unexplained variability in outcomes between Trusts and between patients

• confirm the choice of primary and secondary outcome measures for a full-scale cluster-randomised trial to evaluate effectiveness

• develop and test data collection tools for an economic evaluation within a full-scale cluster-randomised trial

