### Interventions

#### Systematic voiding programme

The intervention will comprise algorithm-driven individualised systematic voiding programmes tailored to the physical and cognitive capabilities of each patient The algorithm specifies two routes: a combined package including bladder training and pelvic floor muscle training for those patients who are cognitively able, and prompted voiding for those with cognitive impairment. Bladder training will include three main components: 1) focused education for patients and carers (including information on the anatomy and physiology of the lower urinary tract, the rationale behind the programme and strategies to suppress the urge to void, for example distraction and relaxation [15,40]); 2) individualised voiding regimens designed to restore normal voiding patterns by progressively lengthening the time interval between voids, based on assessment of participants' normal voiding patterns and self-monitoring; 3) patient-held voiding diary, a cognitive intervention designed to promote self-awareness of voiding habits [41,42].

Pelvic floor muscle training is designed to strengthen types I and II muscle fibres in the pelvic floor. Patients will be instructed to perform 5 fast (3 seconds) and 10-20 sustained (10 seconds) contractions with 10 second relaxation periods between contractions twice a day.

For those patients with cognitive impairments, the programme will consist of elements traditionally classified as prompted voiding: participants will be approached according to individualised schedules (for example every two hours during waking hours), asked if they are wet or dry, and prompted to use the toilet [43]. Verbal praise will be offered for correct reporting of dryness/wetness and successful toileting. Participants with cognitive impairments will be given the opportunity to participate in the education and patient-held diary components of the intervention.

Participants not able to walk to the toilet will be assisted by nursing staff. Participants will be provided with written information about their systematic voiding programme to enable them to continue with it after discharge from hospital.

The intervention has been informed by the findings of an evidence synthesis on the barriers and enablers to successful implementation of conservative interventions for UI completed during the programme's Development Phase, in line with the MRC Framework for developing and evaluating complex interventions [44,45].

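### The fixed covariate list omits baseline cognitive status, although cognition decides the programme route, is already recorded and is plausibly prognostic

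*Protocol article*

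**What the plan says.** The programme has two routes. Under Systematic voiding programme, the algorithm offers bladder training with pelvic floor exercises "for those patients who are cognitively able, and prompted voiding for those with cognitive impairment". The Design section describes the same split.

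The baseline items under Ascertainment of outcomes include "cognitive ability (6 Item Cognitive Impairment Test [62"], with no restriction by arm. Six items in that list carry an asterisk, and the article explains: "The six factors highlighted with a * above from the Edinburgh stroke case mix adjuster [64] will be collected to enhance patient-level adjustment for prognosis". They are age, pre-stroke Modified Rankin Scale, pre-stroke living circumstances, the verbal item of the Glasgow Coma Scale, arm lift and independent walking. The cognitive test has no asterisk.

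Under Data analysis, Outcomes, the individual-level covariates are baseline measures of the outcome where appropriate, followed by "stroke classification, type of incontinence and the other prognostic patient-level information (from the Edinburgh case-mix adjuster) will be included as individual-level covariates". The same section plans "estimates (including 95% confidence intervals) of the effectiveness of each intervention relative to usual care".

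The Objectives include one to "investigate patient-related factors affecting patient outcome".

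**The concern.** The covariate list is worded as a commitment, and it leaves out the one baseline characteristic that determines what an intervention participant receives.

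Three design features make an imbalance in cognition possible:

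- There are only four services per arm.
- The strata use unit configuration, audit performance and admissions, with no patient characteristics (Sequence generation).
- Staff who identify and recruit participants know their service's allocation (Allocation concealment). Patients who cannot consent enter through a consultee, so the recruited share of impaired patients may depend on local practice.

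If impaired participants are more often incontinent at six weeks, a difference between arms in their share moves the estimated effect by the part that the listed covariates do not capture. Adjustment would remove most of that part and could tighten the interval slightly.

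**Working it through.** **The plan's own figure.** The article gives no power calculation; its only sample-size figure is 780. Twelve services admit about 4800 patients a year and 20% are expected to join. A flat 12 months gives 0.20 × 4800 = 960, and a flat 9 months gives 0.75 × 960 = 720. The figure 780 follows if a quarter of admissions fall in the 12-month services: 0.20 × (1200 + 0.75 × 3600) = 780. That split is an assumption, as the article does not give it. Then 780 / 3 = 260 per arm and 260 / 4 = 65 per service.

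**Is cognition covered under another name?** It is neither stroke classification nor type of incontinence, and it is not one of the six Edinburgh factors. Two listed covariates come nearest:

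- "verbal sub-section of the Glasgow Coma Scale [63"] carries an asterisk, but participants must be alert or drowsy, which probably narrows its range, and a verbal item can also reflect aphasia.
- Type of incontinence includes a functional category, which the Background illustrates by motor impairment, depression and aphasia, not cognition.

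Both are partial proxies.

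**Size of an imbalance.** The documents give none of these inputs, so all are assumed: 40% impaired; service-level prevalence with an SD of 5, 10 or 15 points; a 25-point gap in six-week incontinence between impaired and able participants; no other adjustment.

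SD of the arm difference in prevalence = √{2 × (SD²/4 + 0.40 × 0.60/260)}. The shift in the estimated risk difference is that SD × 0.25.

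- Service SD 5 points: √{2 × (0.000625 + 0.000923)} = 0.056; shift SD 1.4 points; chance of a shift beyond 3 points, 3%.
- Service SD 10 points: √{2 × (0.0025 + 0.000923)} = 0.083; shift SD 2.1 points; chance 15%.
- Service SD 15 points: √{2 × (0.005625 + 0.000923)} = 0.114; shift SD 2.9 points; chance 29%.

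A second route uses an intra-class correlation (ICC) for cognition: SD = √{2p(1−p)[1 + 64 × ICC]/260}. With p from 30% to 50% and ICC from 0.02 to 0.10, the SD of the arm difference is 6 to 12 points, and a difference above 10 points has probability 10% to 40%. A 10-point imbalance with an outcome gap of 10 to 30 points shifts the unadjusted estimate by 1 to 3 points.

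**Set against the main effect.** At 50% incontinence and an assumed outcome ICC of 0.05, the 95% half-width is 1.96 × √{2 × 0.25 × (1 + 64 × 0.05)/260} = 17.6 points, so the standard error is about 9.0. The shifts above are about 2%, 5% and 10% of that variance (1.4²/9.0², 2.1²/9.0², 2.9²/9.0²).

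**Could effects by cognition be estimated?** The half-width of the arm-by-cognition contrast is 1.96 × √(4 × 0.25/130) = 17.2 points with an even split, and 1.96 × √{0.5 × (1/104 + 1/156)} = 17.5 points with 40% impaired. This assumes that the contrast does not vary between services. As an illustration, let 60% be able with a 15-point benefit and 40% be impaired with none. The pooled effect is 0.60 × 15 = 9 points, and the contrast of 15 points is smaller than its own half-width.

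**The case against.** The case for leaving the list alone has real strength.

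- The planned models already adjust for several correlates of cognition: age, pre-stroke function and living circumstances, the verbal item, arm lift, walking, type of incontinence and, where appropriate, the baseline outcome. The relevant gap is what remains after these. It is smaller than the assumed 25 points, and nothing in the article lets it be estimated. This stands, so the figures above are upper-end.
- Chance imbalance between services is part of between-service variation, which the mixed model carries in its standard errors. It costs precision and is not hidden bias. This also stands. The exception is differential recruitment by staff who know the allocation. The article monitors patient characteristics across clusters monthly and tabulates baseline data by arm and cluster; that would show an imbalance but not correct the estimate.
- The programme is one algorithm tailored to each patient, and impaired participants are also offered the education and diary components. The effect of the whole programme is a coherent target in a pragmatic trial. This stands: pooling over routes is not an error.
- An analysis of effect by cognition is the kind of detail that an article leaves to the statistical analysis plan, which the Blinding section mentions. Its absence here is therefore no finding.

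A reader might infer that the pilot should, and with an interaction term could, show which route works. The documents do not support that. The contrast has a half-width of about 17 to 18 points, computed with a normal multiplier despite eight services per comparison and with all 260 per arm, although some catheterised participants are to be analysed separately. Nor does the article say that the baseline test sets the route, so effects by test category need not be effects by route.

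None of this explains why a stated covariate list should omit a recorded, plausibly prognostic variable that determines the route.

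**Conclusion.** The omission is real and stands in the protocol's own text. Its consequence is modest: an unadjusted between-arm shift with an SD of about 1.4 to 2.9 points under the assumed inputs, less after the planned adjustment, and mostly within the between-service variance already modelled. The gain from correcting it is a little precision and some protection against differential recruitment.

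The conclusion rests on cognition being prognostic beyond the listed covariates, which is plausible but not shown in the article. It would be wrong to read the point as saying that the pooled estimate is invalid.

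**What to change.** In Data analysis, Outcomes, add baseline cognitive status to the individual-level covariates for the primary and secondary models. Use three categories (able, impaired, not testable), classified from the baseline 6 Item Cognitive Impairment Test in the same way in all three arms, because usual care has no route. Fix the classification in the analysis plan before outcome data reach the statistician. The coefficient for cognition would also serve the objective on patient-related factors.

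Optionally, report each intervention's effect by baseline cognitive status with 95% confidence intervals, labelled exploratory, and state that it is too imprecise to show which route works.

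The cost is one sentence and two extra parameters per model (three categories), with no new data. The downside is that participants who cannot complete the test need their own category.
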